## Abstract

**Background:**

Adolescence is a period of heightened vulnerability to developing mental health problems, and rates of mental health disorder in this age group have increased in the last decade. Preventing mental health problems developing before they become entrenched, particularly in adolescents who are at high risk, is an important research and clinical target. Here, we report the protocol for the trial of the ‘Building Resilience through Socioemotional Training’ (ReSET) intervention. ReSET is a new, preventative intervention that incorporates individual-based emotional training techniques and group-based social and communication skills training. We take a transdiagnostic approach, focusing on emotion processing and social mechanisms implicated in the onset and maintenance of various forms of psychopathology.

**Methods:**

A cluster randomised allocation design is adopted with randomisation at the school year level. Five-hundred and forty adolescents (aged 12–14) will be randomised to either receive the intervention or not (passive control). The intervention is comprised of weekly sessions over an 8-week period, supplemented by two individual sessions. The primary outcomes, psychopathology symptoms and mental wellbeing, will be assessed pre- and post-intervention, and at a 1-year follow-up. Secondary outcomes are task-based assessments of emotion processing, social network data based on peer nominations, and subjective ratings of social relationships. These measures will be taken at baseline, post-intervention and 1-year follow-up. A subgroup of participants and stakeholders will be invited to take part in focus groups to assess the acceptability of the intervention.

**Discussion:**

This project adopts a theory-based approach to the development of a new intervention designed to target the close connections between young people’s emotions and their interpersonal relationships. By embedding the intervention within a school setting and using a cluster-randomised design, we aim to develop and test a feasible, scalable intervention to prevent the onset of psychopathology in adolescence.

**Trial registration:**

ISRCTN88585916. Trial registration date: 20/04/2023.

**Supplementary Information:**

The online version contains supplementary material available at 10.1186/s13063-024-07931-2.

## Background

Existing research into potential mechanisms underlying mental health problems has typically had a narrow focus, usually examining a limited number of key processes and outcomes within a single disorder [1]. However, approaches focusing on a single process or outcome do not reflect the complexity and interconnectedness of the processes contributing to mental health difficulties in adolescence. Parallel to this, a significant limitation of past treatment and prevention work has been the focus on disorder-specific interventions. Yet, compelling evidence indicates that (a) the structure of mental health symptoms does not straightforwardly map onto traditional diagnostic categories; (b) comorbidity is high; and (c) individuals may experience multiple shifts from one diagnosis to another over time [2]. In that context, the *prevention* of adolescent mental health problems is a particularly complex challenge because it is often not possible to predict in advance which disorder(s) should be targeted and indeed young people may be at risk for more than one. In recognition of these challenges, attention is shifting to the development of transdiagnostic approaches to treatment and prevention [2]. The transdiagnostic approach aims to target common cross-disorder mechanisms, rather than specific diagnoses. This approach is consistent with the recent evidence that vulnerability to mental health difficulties can be represented by a General Psychopathology dimension (the ‘p-factor’), which emphasises the action of cross-disorder vulnerability mechanisms that predispose to overall poor mental health [3].

There is considerable evidence that *emotional processing* and *social relationships* are fundamental—and closely interlinked—transdiagnostic mechanisms underpinning resilience and vulnerability to mental health problems in adolescence [2–5]. Emotion processing and regulation mechanisms implicated in poor mental health continue to develop during adolescence [6]. Adolescence also represents a major developmental shift during which young people are exposed to changing social environments that must be navigated with increasing independence from family. Peers become more, and parents become less, significant [7]. Succeeding at navigating these new social challenges is crucial for ongoing mental health and wellbeing [7]. Prior work has established an association between emotion processing and mental health/wellbeing, and between social relationships and mental health/wellbeing [8]. Yet, little research has systematically investigated how adolescents’ emotion processing might actively shape their social relationships with peers or how social relationships with peers shape adolescent emotion processing in ways that either predispose to or protect against mental health problems.

In the proposed intervention, we focus on emotion processes (specifically negative emotion perception and emotion regulation) and social relationships as promising transdiagnostic targets for a preventative, indicated intervention. Further, we focus on schools with a higher-than-average incidence of poverty, in recognition of the increased risk for mental health problems in economically deprived populations [9]. Such interventions are particularly timely in the context of recent large-scale trials that have failed to find evidence to support the effectiveness of universal interventions [10, 11]. This paper details the protocol of the randomised controlled trial to test the efficacy of the ‘Resilience through socioemotional training’ (ReSET) intervention at reducing psychopathology in adolescents.

### Cognitive mechanisms

Targeted training can be applied to improve specific transdiagnostic emotional or cognitive processes under tightly controlled experimental conditions. There is good evidence that such training can alter emotional processes (including those selected for this intervention) and may positively influence mental health, in line with the presumed causal role of these mechanisms (e.g. [12]). In this study, we focus on training key cognitive-emotional processes that have been associated with the development of psychopathology in childhood and adolescence.

Sensitivity to perceiving negative emotions, especially sadness and anger, has been linked to several mental health conditions, including depression, anxiety and disruptive behaviour disorders [13–15]. Negative emotion perception is commonly measured by assessing sensitivity in perceiving sadness and anger [16]. Lower thresholds for perceiving negative affect are thought to impact adolescents’ own emotional state, as well as the formation and maintenance of their social relationships [17]. Indeed, a biased perception to perceive negative affect in others can lead adolescents to choose hostile responses, which in turn provoke negative responses from other individuals, thereby reinforcing biased emotion perception in a ‘vicious cycle’ [14, 15, 18]. However, previous research has demonstrated that negative emotion perception is amenable to intervention, interrupting the cycle of negative reinforcement between biased emotion perception and hostile patterns of responding. For example, training to increase adolescents’ threshold for perceiving negative affect has been found to improve symptoms of depression [19].

A further emotion process implicated in mental health conditions is emotion regulation, which refers to implicit and explicit processes and strategies involved in regulating emotional states (i.e. suppression, distraction, reappraisal; [20]). Adolescence is a sensitive period for emotion regulation development, with many individuals improving their use of adaptive emotion regulation strategies during this period [21, 22]. However, individual differences in the development of emotion regulation abilities are associated with risk for psychopathology in adolescence [23] and indeed poor emotion regulation skills in earlier childhood are associated with enduring mental health across childhood and adolescence [24]. Adequate downregulation of negative emotional states during childhood and adolescence plays a critical role in adaptive development and well-being [25] as in the quality of social relationships [26]. Importantly, emotion regulation difficulties and maladaptive regulation strategies have been associated with risk for psychopathology in children and adolescents [27], in particular internalising symptoms [28], anxiety disorders and disruptive behaviour disorders [13]. Consistent with the view that emotion regulation is implicated in the onset and maintenance of psychopathology, training that increases the use of adaptive regulation strategies (e.g. reappraisal and temporal distancing) can decrease symptoms of anxiety in adolescents [29]. However, previous interventions (e.g. [29]) have consisted of only a single session and improvements have not been sustained over longer periods of time in these studies. Interventions that have observed long-term effects of training emotion regulation typically utilise several sessions (e.g. [12]). To date there is tentative evidence that adolescents’ use of adaptive emotion regulation strategies can be increased, though it may be necessary to train these abilities over a number of sessions to see lasting benefits. This is the approach we take in the present intervention.

A considerable body of research has highlighted the links between interoception, the perception of the body’s internal state, and the ability to perceive and regulate emotions [30]. Further, interoceptive ability has been associated with several mental health outcomes, including anxiety, depression, alcohol and substance abuse [31–33]. It has been suggested that interoception may represent a common, transdiagnostic, vulnerability factor for psychopathology (i.e. that individual differences in interoception may contribute to ‘p-factor’ development; [34]). Recent theoretical work has also suggested that the rise in psychopathology observed in adolescence may be, in part, attributable to interoceptive impairments during this period [31, 34]. To examine the mediating role of interoception in the intervention outcomes, we measure interoceptive attention and accuracy before and after the intervention.

### Social relationships in adolescence

Social relationships, particularly peer relationships, are vitally important for mental health and wellbeing during this developmental period [35]. Recent meta-analytic work has documented robust associations between the number of peer friendships adolescents have, as well as their perceptions of these relationships, and mental health [36, 37]. For example, young adolescents with fewer friendships, or those with poorer-quality friendships, present greater internalising and externalising symptoms than those with more friends [36, 37]. Additionally, rejection and exclusion from the peer group engender loneliness and diminished self-esteem and increase risk for anxiety and depression [38–40]. Friendships are also more likely to break down when an adolescent experiences depression [41]. These studies suggest that peer friendships have a bi-directional relationship with mental health during adolescence.

While adolescence is a period in which the individual spends increasing time with peers and less time with parental figures (e.g. mothers, fathers, step-mothers, step-fathers or foster parents; [42]), the relationships between adolescents and parental figures are nonetheless important for mental health outcomes. Insecure parental attachment predicts conduct problems and emotional difficulties during adolescence [43], suggesting that parental attachment is a transdiagnostic risk factor for psychopathology. Further, positive relationships with caregivers are associated with positive mental health outcomes and wellbeing [44]. Indeed, positive relationships with parents and caregivers can also act as a protective factor from other social stressors, such as peer victimisation [45]. As such, a hybrid intervention focussing on improving the quality of social relationships along with training emotion processing skills implicated in mental health disorders could present an effective approach to the prevention of psychopathology in adolescence.

Inter-Personal Therapy (IPT) is an established evidence-based therapy that specifically focuses on improving interpersonal functioning and social relationships and was originally developed to treat depression [46]. This treatment has been adapted as a group intervention for adolescents (IPT-AST), which focuses on interpersonal problems young people may be experiencing, supports adolescents to recognise their feelings and link these to interpersonal conflicts in their relationships, and promotes interpersonal connections, social problem solving and communication skills [47]. Individual and group IPT-AST have good evidence of efficacy for depression in young people [48] and crucially there is increasing evidence for its effectiveness for a broad range of mental health outcomes [49, 50].

### Objectives

Addressing the cyclical relationship between relationships, emotion processing and mental health presents one potentially fruitful way to prevent the onset of psychopathology in adolescence. There is considerable evidence that intra-individual mechanisms related to emotional processing and inter-individual mechanisms linked to social relationships are both crucial for understanding risk for mental health problems in adolescence. However, little work has bridged the disciplinary boundaries between these approaches. Similarly, while interventions have been developed either to alter emotional processing mechanisms or to improve social relationships, these two approaches to intervention have been developed in almost complete isolation from one another and often fail to incorporate the views of those at whom the intervention is aimed. By working with clinicians, cognitive neuroscientists and young people themselves we aim to develop a novel prevention programme that specifically focuses on the close connections between emotional processing and social relationships. The integration of these two approaches to intervention could yield great scientific and clinical benefits and provide a much-needed new approach to mental health prevention for young people.

The aim of the current study is to test the impact of a novel hybrid prevention programme for young people, targeting key cognitive-emotional and social mechanisms. Specifically, we will test whether this novel hybrid intervention leads to better mental health and well-being outcomes in at-risk adolescents (highest 25% of general psychopathology risk), compared to those in a non-intervention arm. Further to this aim, we will examine whether the intervention’s impact on mental health and wellbeing is mediated by changes in emotional processing and social relationships. Our key hypotheses are as follows:(1) Our novel hybrid programme will lead to better mental health and well-being outcomes in at-risk adolescents (highest 25% of psychopathology risk), compared to those in the non-intervention arm.(2) The impact of the hybrid intervention will be mediated, in part, by changes to emotion processing and social relationships; specifically, the impact of the intervention will be mediated by:A shift in emotion perception to view fewer faces as hostile.A better ability to regulate emotions when presented with negative stimuli.Improved interoceptive ability.Improved peer acceptance and attachment with friends and parents, as well as decreased peer victimisation.

### Trial design

The ReSET intervention is a cluster randomised, controlled, multicentre superiority trial with (1:1) randomisation. The randomisation schedule will happen at the school year group level, meaning in each school we will have a younger and older cohort. As our study period will span two academic years, some baseline data collection and some intervention groups will take place in the following school year. In each school, one cohort is allocated to the hybrid intervention arm and the other to the non-intervention control arm; this is balanced across participating schools using block randomisation. Researchers are blind to participants’ group allocation during data collection. The intervention consists of eight group sessions, as well as one pre-group and one mid-group session that is completed individually or with the attendance of a parent or carer. All group sessions are 90 min in length, while individual sessions are 60 min each.

## Methods

### Study setting

Participants will be recruited from mainstream, state secondary schools in the South East of England. Intervention sessions will take place within the participants’ schools in a classroom designated by the host school.

### Eligibility criteria

Eligible participants will include pupils who are initially in years 7–9 (ages 11–14) at the time of the first baseline assessment, with each school running the study across 2-year groups only (i.e. either years 7 and 8, or years 8 and 9). We will seek consent from parents or carers, and the participant before they are enrolled in the study. Young people at *elevated risk* of mental health problems will be invited to participate, where *elevated risk* is operationalised as having a self-reported SDQ Total Difficulties score of 15 or higher in our screening assessment. This corresponds approximately to selecting the top 25% of this age group in the UK (see ‘Outcomes,’ below for a description of this measure). This estimate is based on self-reported SDQ scores from 2100 UK adolescents aged 10–15 derived from the Understanding Society panel survey (see [51]). The 75th percentile of the SDQ Total Difficulties Score in this sample was 15. Students will be considered ineligible if they have high rates of school absence or are identified by the school as being inappropriate for the group intervention due to a high risk of harm to self or others. We will not exclude participants on the basis of neurodivergence, such as Autism and ADHD, though pre-existing diagnoses will be recorded during the study, as will participants’ use of other mental health services.

Schools will be eligible to participate if more than 30% of their pupils qualify for free school meals (Department for Education, 2022). We chose this criterion to ensure socioeconomic diversity in our sample. A record of study sites can be found at: https://www.isrctn.com/ISRCTN88585916.

Facilitators will be mental health professionals either working for schools (e.g. school counsellors) or mental health professionals that provide services within schools from external agencies (e.g. NHS Educational Mental Health Practitioners). All facilitators will attend a 2-day training course (delivered by the clinical lead, RL, and a member of the research staff, AL) to provide them with information about the intervention, opportunities to roleplay group sessions, and training on how to administer the cognitive training tasks. Facilitators will have weekly supervision with the clinical lead, RL, throughout the duration of the intervention.

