#### Adherence

Adherence to the intervention is promoted using verbal encouragement from school contacts who will liaise between the facilitation team and study participants. School liaisons also communicate with class teachers to ensure students are released from their usual classes to attend sessions. Further, the mid-group meeting is used as an opportunity to identify any barriers to participation and, should any barriers be identified, provide additional support to increase adherence. Participants’ adherence to the researcher assessments is encouraged by remunerating participants for these sessions.

Throughout the intervention, adherence is monitored by recording attendance as well as monitoring the cognitive training data collected in each group session. This monitoring protocol includes attention measures collected during the cognitive training tasks. In the emotion regulation training task, participants are asked at three timepoints to report how engaged they were feeling to indicate their adherence to the training. For the interpretation bias training, participants are asked to repeat the first 45 trials measuring their balance point if they incorrectly identify the emotion in more than three of the extreme morphs. For example, if a participant incorrectly identifies the extreme image expressing anger as ‘happy’ more than three times, they are asked to repeat the assessment phase. We will report data on participants who are asked to repeat the assessment phase as a measure of adherence to the interpretation bias training.

Finally, at three timepoints during the intervention (group sessions 1, 2 and 5) a member of the research team conducts an audit of the group session. This process involves a member of the research team attending the session to monitor fidelity to the intervention manual, assessing whether key concepts are covered and explained using terminology described in the manual using an adherence checklist. The audits are also used to identify interpersonal dynamics within the group that may affect adherence to the intervention (e.g. challenging behaviour).

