## Assignment of interventions

### Timing of randomisation

Randomisation will be performed at each school once that school has been provided with a list of participants scoring within the top 25% (i.e. above the cut-off score of 15) of the sample from both year groups. All eligible students will be invited to participate, and students will be randomised in each year group in a numerical order: (a) 1–10 (Group 1)—Term 1, (b) 11–20 (Group 2)—Term 2, and (c) 21–30 (Group 3)—Term 3. As our intervention runs over two academic years in some schools (April 2023–March 2024), some cohorts will transition to the next academic year before the completion of the intervention. For example, the group that is in year 7 when the school is randomised will be in year 8 during the final intervention group run in that school (January–March 2024).

A random selection of eligible adolescents will subsequently be invited to participate in the main study. Parents will receive consent forms detailing the aims of the study, the structure of the intervention and the time commitment expected of participants (see Additional file 1: Appendix), which will also include a consent form. Once parental consent has been obtained, participants will be randomly allocated to one of the three school terms (i.e. the sample will be split into thirds with one third taking part in term 1, a second third taking part in term 2, and the final third taking part in term 3). At the beginning of the allocated term, consent will be sought from the young person, and they will complete the assessment battery comprising of mental health, emotion processing and social relationship measures (see Fig. 4). Participants allocated to the intervention arm of the study will then complete 10 sessions inclusive of individual pre-group sessions, 8 weekly group sessions, and a mid-group session. Participants allocated to the control arm of the study will complete their usual classroom schedule.

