**Fig. 4 Fig4:**

Schematic of the project timeline

Procedures are also in place to account for drop-out of participants. Should any young people drop out before the intervention has begun (prior to the one-to-one meeting with the group facilitator), the next consecutive student in the list will be invited to take their place (i.e. student 31, student 32, etc.) and baseline assessments will be conducted. On the other hand, any students who ‘drop-out’ between baseline assessment and intervention will be treated as ‘intention to treat’ and therefore will be invited to take part in the follow-up assessment even if they do not participate in the ReSET group.

For the integrity of the randomisation to be preserved, it is crucial that the allocation of young people to a treatment within a given school occurs *after* all eligible children from that school (and their parents) have been screened and consented to take part. If a child or a parent knew, at the point of baseline assessment and/or at the point of making the decision whether to take part, which treatment arm they would be signing up for, then participation would not be independent of randomisation. This would risk selection effects which have the potential to cause bias in the estimation of intervention effects. As such, we will screen the entirety of the participating year groups at the first screening timepoint, and students will only be informed which group they have been allocated to only after they have completed their baseline assessment. We expect modest increases in symptomology between the screening phase and the beginning of the third set of assessments in line with population-level changes to psychopathology during adolescence (e.g. [95]). However, it is vital to the randomisation procedure that participants and their parents consent to take part in the study *prior* to when randomisation takes place, which necessitates that we screen and consent participants in the top 25% of SDQ scores at a single timepoint. We will collect SDQ data at our baseline assessment in addition to this screening questionnaire, which will allow us to adjust for changes to general psychopathology between the first screening timepoint and when the participant completes the baseline assessment.

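### The school's own exclusions are not fixed before allocation, and the two accounts of randomisation order conflict, so exclusion could differ between arms

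*Protocol article*

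**What the plan says.** **Who is excluded.** Eligibility criteria makes a pupil ineligible for frequent school absence, or if "identified by the school as being inappropriate for the group intervention due to a high risk of harm to self or others". The wording applies to all pupils. The section does not say when the judgement is made, or whether the arm is known at that point.

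**What is allocated.** Trial design: "In each school, one cohort is allocated to the hybrid intervention arm and the other to the non-intervention control arm". Whole year groups are therefore the units.

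**First account of the order (Timing of randomisation, opening paragraphs).** "Randomisation will be performed at each school once that school has been provided with a list of participants scoring within the top 25" per cent of the sample. Then: "A random selection of eligible adolescents will subsequently be invited to participate in the main study". Parental consent follows, then random assignment to one of three terms, and then: "At the beginning of the allocated term, consent will be sought from the young person".

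**Second account (same section, after the Fig. 4 caption).** Allocation within a school must come after "all eligible children from that school (and their parents) have been screened and consented to take part". The section adds that "students will only be informed which group they have been allocated to only after they have completed their baseline assessment".

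**Replacement and intention to treat (same section).** A pupil who drops out before the one-to-one meeting with the facilitator is replaced by the next pupil on the list. A pupil who drops out between baseline and intervention is followed up under intention to treat.

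**Who knows the arm.** Blinding limits knowledge of allocation to the independent statistician, the research coordinator and the principal investigators, but foresees disclosure by school staff. Adherence says: "School liaisons also communicate with class teachers to ensure students are released from their usual classes to attend sessions".

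**The concern.** The second exclusion asks whether a pupil is fit for a group that, within a school, only one year will attend. Staff who already know which year that is are answering a practical question for one cohort and a hypothetical one for the other. The same nominal standard can then be applied differently in the two arms.

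This is not the same as the order of family consent and randomisation. Even if every family consented first, a later exclusion by the school could still remove pupils from one arm only. The pupils concerned are those at higher risk of harm or often absent, so their loss could change the prognosis of that arm. Both primary comparisons, SDQ Total Difficulties and mental wellbeing, would be exposed. Baseline adjustment deals with what the baseline score carries, but not with prognosis tied to absence or risk of harm beyond that score.

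**Working it through.** **Step 1. Set the two accounts side by side.**

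| Event | First account | Second account |
|---|---|---|
| Trigger for allocation | School has the list of pupils above the cut-off | All eligible children and parents screened and consented |
| Invitation | After randomisation | Before allocation |
| Young person's consent | Start of the allocated term | Before allocation |
| School's exclusions | Not placed | Not placed; implied at most by the word eligible |

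Both cannot hold. Young people who consent at the start of Term 2 or 3 have not all consented before their school is allocated. The reason given for the second account is what a child or parent might know; school staff are not mentioned.

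**Step 2. Trace a pupil due in Term 2 or 3.** Staff release pupils from class for sessions, and facilitators may be school counsellors. Once Term 1 groups run, staff can see which year has the intervention. Because arms are whole years, they then also know the arm of every pupil still to enter. If the school rules such a pupil out before baseline, the replacement rule applies and the intention-to-treat sentence does not. A pupil lost after baseline but before the one-to-one meeting falls under both rules. Reserve pupils enter when the arm is already set.

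**Step 3. How many pupils enter late.** The plan expects 30 pupils per school year in three sets of 10, over nine schools. Entrants in Terms 2 and 3 number 20 × 9 = 180 of 270 per arm.

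**Step 4. Illustrative size.** The plan gives no exclusion rate, so there is no stated figure to reproduce for this point. Inputs from Preliminary considerations: eligible mean 19.1, SD 3.6, target difference 1.5 points (1.5/3.6 = 0.42, as the plan states). Assumed: a fraction f of one arm is excluded, with mean SDQ m, and no such exclusion in the other arm. The 19.1 comes from a national survey and stands in here for the arm's mean.

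Shift in the arm's mean = (19.1 − f·m)/(1 − f) − 19.1 = −f(m − 19.1)/(1 − f)

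| f | m | Calculation | Shift (points) | Share of 1.5 |
|---|---|---|---|---|
| 0.05 | 22 | 0.05 × 2.9 / 0.95 | −0.15 | 10% |
| 0.05 | 25 | 0.05 × 5.9 / 0.95 | −0.31 | 21% |
| 0.10 | 22 | 0.10 × 2.9 / 0.90 | −0.32 | 21% |
| 0.10 | 25 | 0.10 × 5.9 / 0.90 | −0.66 | 44% |

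A wider range, with f from 2% to 10% and m from 22.7 to 26.3 (1 to 2 SD above 19.1), gives 0.02 × 3.6/0.98 = 0.07 to 0.10 × 7.2/0.90 = 0.80 points, or 5% to 53% of the target.

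For scale, 5–10% of 270 is 13.5–27 pupils. If all were Term 2 and 3 entrants, that would be 7.5–15% of the 180, so the upper end needs a high late exclusion rate.

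**Step 5. After baseline adjustment.** With the plan's baseline-to-outcome correlation of 0.5 as the adjustment slope, and a baseline shift s:
- If exclusion follows the measured baseline score, the outcome shifts by 0.5s and adjustment removes 0.5s. Nothing remains.
- If exclusion follows stable underlying severity reflected equally at both times, the outcome shifts by s and adjustment removes 0.5s. Half remains: 0.15/2 to 0.66/2, about 0.08–0.33 points, or 5–22% of 1.5.
- If exclusion follows other prognostic factors, such as absence, more could remain. The documents give nothing with which to size this.

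**The case against.** The strongest reply is that a lock exists. The second account calls it crucial that allocation follows screening and consent of all eligible children, and eligibility already includes the school's exclusions. Followed strictly, this would largely close eligibility first. So a reader who infers that nothing stands between allocation and the school's judgement goes too far. What stands is that the first account contradicts this safeguard, and that the safeguard neither names the school's judgement nor bars a later one.

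Blinding also restricts who knows the allocation, and no passage says staff know the arm when they judge eligibility. That is correct for the time of the list. It cannot hold in a school once groups are running. Schools could also apply both criteria from their own records before any list arrives, but the plan does not require it.

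A reader might infer bias towards benefit, on the view that staff would keep difficult pupils out of the group. The documents do not support that. The criterion is worded for every pupil, and staff might equally want the neediest pupils to get the group, which would reverse the direction.

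The 0.15–0.66 points are a shift in baseline mean, not bias in the adjusted estimate, and the exclusion rates are assumed. This is accepted.

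Finally, a journal article may leave operational timing to the full protocol. Silence alone would not be a finding. Here the article gives two incompatible orders, together with a replacement rule that leaves the gap open.

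**Conclusion.** The point holds as a gap in the protection of randomisation. The school's exclusions are not tied to a moment before allocation, the two accounts of the order conflict, and the replacement and intention-to-treat rules do not protect a pupil whom the school rules out before baseline. Differential exclusion is possible under the rules as written; the documents show neither that it occurs nor its direction.

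The size is illustrative only. A one-arm exclusion of 5–10% with mean SDQ 22–25 moves that arm's baseline mean by 0.15–0.66 points (10–44% of the 1.5-point target) before adjustment. What remains after adjustment runs from nothing to about 0.33 points under the two simple models above, and could be more if exclusion tracks prognosis that the baseline score misses. No corresponding figure is offered for wellbeing. This should be corrected, but it does not by itself invalidate the design.

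**What to change.** 1. Reconcile the two accounts in Timing of randomisation so that one order of screening, exclusion, invitation, consent and allocation is stated.
2. In Eligibility criteria and Timing of randomisation, state that the school applies both exclusions to the full lists of both year groups, including reserve pupils, on one form and to the same standard. It returns the locked lists before the trial manager releases that school's allocation.
3. State that no pupil is removed from the trial, or replaced, on these grounds afterwards. A pupil later judged unsuitable for the group is handled under the existing safeguarding rules, and stays in follow-up and in the intention-to-treat analysis.
4. Report the number excluded and their screening SDQ by arm.

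None of this changes the exclusion criteria themselves. The cost is wording, one form per school (nine schools) and a few days' delay per school before allocation is released. No extra pupils are needed.
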